**Fig. 1 Fig1:**
[figure not shown]
Schematic of the cross-over study design. Interested individuals will first perform an eligibility assessment to determine whether they can be consented into the study. Once 35 residences have been recruited (between 35 and 70 participants), participants will be randomized into two cohorts and experience three lighting conditions (L1, L2, L3). Lighting conditions are described in more detail in the “Environmental Lighting Conditions” section

Before starting the first lighting condition (L1 or L2 depending on the cohort), a baseline period lasting approximately 2 weeks will be used to characterize the lighting quality of each participants residence. The lighting in the baseline period will be set to match as closely as possible the lighting that was previously installed. Throughout the baseline, participants will be instructed to use the light as they normally would.

The L1 lighting condition and the baseline condition will have the same lighting parameters and will be configured to match the residents existing lighting prior to installing the current lighting system. Participants will be instructed to keep the lights all the time while awake during the duration of the study, however we gave individuals flexibility to wake up when they naturally did to not disrupt their sleep patterns by shifting to a rigid wakeup schedule.

After each 4-week lighting condition of the cross-over design, participants will experience a 1-week “washout” period during which they will experience the same lighting as the baseline period (L1 condition). After completing the cross-over and subsequent washout period, participants will experience the L3 condition to determine if there is a saturation effect of how much morning blue-rich light is needed to affect the health-related measures of interest.

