**Fig. 2 Fig2:**
[figure not shown]
24-hour schedule of lighting parameters for **a**) L1, **b**) L2, and **c**) L3 lighting conditions. L1 is designed to be a static light condition similar to what residents would typically have in their independent living residences. L2 and L3 are designed to have increased EML in the morning hours with more exposure to blue-rich light and also slightly decreased EML in the evening hours

L1: static lighting condition with fixed CCT and brightness;L2: dynamic lighting condition with dynamic CCT and brightness; and.L3: dynamic lighting condition similar to L2 but with increased brightness in the morning hours.

The light bulbs installed in each residence will be programmed and controlled using the Philips Hue Application Programming Interface (API). Each lighting condition will be implemented to achieve minimum levels of equivalent melanopic lux (EML, measured in mlux) while ensuring high levels of blue-rich light in the morning and low levels of blue-rich light in the evening. EML quantifies the circadian effect from the light source by weighting the response from ipRGCs [90, 91]. Recent studies have suggested EML is a favorable indicator of the melatonin suppression response [37, 38, 92]. A minimum EML of 280 melanopic lux (mlux) for at least 4 h during the daytime is recommended as an optimal circadian stimulus that normalizes biological responses such as melatonin suppression, circadian phase resetting, and subjective altering responses [39, 93]. As shown in Fig. 2, the L1 condition is designed to have a fixed EML throughout the 24-hour period, whereas the L2 and L3 conditions provide a cycle of gradually higher EML during the morning and lower EML in the evening. As such, the mlux values in the morning are greater in L2 and L3 compared to L1 (and less in the evening for L2 and L3 compared to L1). Guidelines provided by the WELL Building Standard were taken into consideration when selecting the EML levels for each lighting condition [93].

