### Statistical analysis plan

Using data from both wearable devices and surveys, the primary comparison will be within-person change in sleep quality scores between each of the three lighting conditions (L1, L2, L3) and the same scores measured during the baseline period. The L1 condition serves as an active control condition as this is the same lighting as they would typically experience in the baseline condition. The secondary comparison will be to compare changes in physical activity, heart rate, and survey data across each lighting condition pair. Data collected during the baseline period will also be compared against the L1 condition to determine whether asking participants to change their behavior with the lights (e.g., do not turn the lights off) affects any of the dependent variables of interest, thereby ensuring that any health benefits seen in the dynamic conditions relative to the static condition are likely reflective of improvements over participants lighting as usual. Participants who are eligible only because their partner is eligible will be analyzed separately.

We will use generalized estimating equations to account for the longitudinal repeated-measures design and handle missing data. For the surveys and cognitive assessments, there will be a minimum of 8 measurements per lighting condition (two cognitive assessments per week for four weeks). If only 35 participants are enrolled, we expect 80% power to detect a difference of minimum of 0.45 standard deviations. Conversely, if we have 70 participants enrolled (i.e., all the rooms are double occupancy with both persons eligible) we expect 80% power to detect a minimum difference of 0.3 standard deviations. For either of these scenarios, we expect to be able to detect at least 0.3 standard deviations, yielding sufficient power, even for the relatively infrequent cognitive assessments. To minimize missing data,, we will monitor key metrics (such as response rates) throughout the study using IRB-approved approaches to encourage participation. As a rule of thumb, participants who complete the study with greater than 50% missing data on any outcome measure will not be included in the relevant final analysis population.

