## Discussion

We are presenting a novel research protocol to assess how indoor lighting affects several measures of brain health in older adults living in independent living residences. Preservation of brain health is an important component in maintaining function and independence. Many studies of the health benefits of different lighting conditions have focused on individuals who have already developed dementia in assisted living facilities. Our focus here is to understand how similar lighting interventions might be effective at promoting different measures of brain health which have been shown to help mitigate health-risks before the onset of dementia may occur [24]. Understanding how indoor lighting might affect or even improve multiple measures of brain health, such as sleep, physical activity, social engagement, and mood could have significant implications for guiding older adults to maintain their health and well-being as they age.

The design of this study also provides an innovative approach to providing a control to compare against for each condition. The L1 (static lighting) condition will be designed to match as closely as possible the lights that participants initially had installed. However, participants will need to change their behavior during each of the lighting conditions (L1, L2, L3), making the L1 condition an active control condition. Activity recorded during the baseline period during which participants can turn on/off their lights as needed will also be compared with activity recorded during each of the lighting conditions to determine how much of an effect exists during the active control (L1) condition.

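### Comparing baseline with L1 cannot ensure that a gain of L2 over static lighting is a gain over lighting as usual; outside sleep and activity, that reading needs the direct L2 minus baseline contrast

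*Protocol article*

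**What the plan says.** L1 and the baseline period share the same lighting parameters (Study design). They differ in how the lights are used. In baseline, residents use them as they normally would. Afterwards, "Participants will be instructed to keep the lights all the time while awake during the duration of the study", which I read as keeping the lights on. The Discussion accepts the consequence: "participants will need to change their behavior during each of the lighting conditions (L1, L2, L3), making the L1 condition an active control condition".

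The Statistical analysis plan section then states: "Data collected during the baseline period will also be compared against the L1 condition", to see whether the changed behaviour affects the outcomes. It presents this as "ensuring that any health benefits seen in the dynamic conditions relative to the static condition are likely reflective of improvements over participants lighting as usual".

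Three other statements bear on the point:
- The primary comparison is the within-person change in sleep quality from baseline to each of L1, L2 and L3 (Statistical analysis plan).
- Physical activity, heart rate and survey data are compared between pairs of lighting conditions (same section). The central hypothesis is tested for every measure as L2 against L1 (Study design).
- The Discussion compares baseline activity with every lighting condition, to see how much of an effect exists in L1.

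**The concern.** The plan bases a statement about L2 and usual lighting on a comparison that does not include L2. Its conclusion holds only if L1 is no worse than baseline by an amount that matters, and comparing the two does not make that so. If the lights-on regimen worsens an outcome by as much as L2 exceeds L1, residents under L2 are no better off than in ordinary life.

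The protocol's own text makes some worsening conceivable. L1 holds a fixed level through the day, whereas evening light is lower under the dynamic conditions ("and less in the evening for L2 and L3 compared to L1"), and L1 lights stay on for all waking hours. The Background links less blue light at night with better sleep, and light outside the natural pattern with sleep-wake problems. The study aims to inform residential lighting, so the comparison with usual lighting is the one readers will take away.

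**Working it through.** **Inputs.** From the Statistical analysis plan section: "If only 35 participants are enrolled, we expect 80% power to detect a difference of minimum of 0.45 standard deviations"; with 70, "we expect 80% power to detect a minimum difference of 0.3 standard deviations". From Study design: baseline lasts about 2 weeks and always comes first; each condition lasts 4 weeks. Assumed, because not stated: two-sided 5% tests, and an L1 worsening of 0.3 SD. The 0.3 SD is the plan's smaller detectable difference used as an illustration, not an expected harm.

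**1. The plan's own figures.** The simple paired formula is d = (z_α + z_0.80)/√N, with SD meaning the SD of the within-person difference.
- Two-sided 5%: 2.802/√35 = 0.474 and 2.802/√70 = 0.335.
- One-sided 5%: 2.486/√35 = 0.420 and 2.486/√70 = 0.297.

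The plan gives 0.45 and 0.30. Neither convention reproduces both, and the significance level, sidedness and within-person correlation are not given. I therefore take the stated values at face value and derive the standard error from them.

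**2. Implied standard error of a within-person contrast.** SE = d/2.802, so 0.45/2.802 = 0.161 SD (N = 35) and 0.30/2.802 = 0.107 SD (N = 70).

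**3. Chance that baseline against L1 is non-significant when L1 is truly worse by w.** This is Φ(1.96 − w/SE), the opposite tail being negligible.

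| w | N = 35 | N = 70 |
|---|---|---|
| 0.2 SD | 76% | 54% |
| 0.3 SD | Φ(1.96 − 1.87) = 54% | Φ(1.96 − 2.80) = 20% |
| 0.45 SD | 20% | 1% |

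With one-sided 5% tests instead, the N = 35 standard error is 0.45/2.486 = 0.181, and 0.3 SD is missed Φ(1.645 − 1.657) ≈ 49% of the time. N = 70 stays at 20%.

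A result that only just fails significance has a 95% interval reaching a worsening of 2 × 1.96 × SE: 0.63 SD (N = 35) or 0.42 SD (N = 70).

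**4. What this could do to the claim.** I simulated period means with variance SE²/2 each, so that every contrast has the SE above. True values were baseline 0, L1 −0.3 and L2 0, meaning no gain over usual lighting. The plan states no decision rule, so the first row supposes a reader who treats a non-significant baseline–L1 result as clearance.

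| Probability of a false claim over usual lighting | N = 35 | N = 70 |
|---|---|---|
| L2 − L1 significant, baseline–L1 not | 17% | 11% |
| Same, baseline variance doubled (assumption, for its shorter length) | 25% | 25% |
| L2 − L1 and L2 − baseline both significantly favour L2 | 2% | 2.5% |
| Previous row, with an assumed favourable 0.2 SD drift after baseline | 17% | 43% |

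Under that drift, the first row rises to 39% and 65%. The direct contrast is therefore better than the bridge through L1 in both settings, but its low error rate holds only without a time trend.

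**The case against.** The case against is substantial, and much of it stands.

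- **Sleep and activity are already covered.** The mechanism for harm is mostly about sleep, and there L2 is compared directly with baseline. A gain that only recovered an L1 loss would show as no gain over usual lighting. The Discussion gives activity the same comparison. This stands and limits the point.
- **The text is hedged and states no significance rule.** It says *likely*, and the Discussion speaks of how much of an effect exists, which is estimation. So the 17% and 11% describe a reading of the plan, not a rule in it. A margin or bound could also sit in an analysis plan that is not shown, and its absence from the article is no fault.
- **Direction and size are assumed.** Nothing in the protocol says L1 is 0.3 SD worse than baseline. More daytime light could make L1 better, in which case L2 − L1 would understate the gain over usual lighting.
- **The direct contrast is not randomised.** Baseline is always first and the cognitive tasks are repeated twice weekly, so drift and practice enter L2 − baseline.

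A reader might go further and infer that an L2 − L1 benefit could itself be an artefact of the control. The documents do not support that. The lights-on instruction applies to L1, L2 and L3 alike, and the order of L1 and L2 is randomised. Only the reading of that contrast as a gain over usual lighting is at risk.

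None of this rescues the ensuring clause. It covers any health benefit, and for heart rate, non-sleep surveys and cognition the baseline–L1 comparison is the only stated link to usual lighting.

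**Conclusion.** The point holds in limited form. The baseline–L1 comparison can estimate the effect of the lights-on instruction; it cannot ensure that gains over static lighting are gains over usual lighting. At the plan's own detectable differences, it would miss an assumed 0.3 SD worsening about 54% of the time with 35 participants and 20% with 70. These rates assume two-sided 5% tests and a baseline mean as precise as a condition mean, so the shorter baseline probably makes them optimistic. The consequence falls on the wording of conclusions for outcomes other than sleep and activity. The randomised L2 − L1 test of the central hypothesis is unaffected.

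**What to change.** In the Statistical analysis plan section:
1. Delete the clause beginning *thereby ensuring*.
2. Keep randomised L2 − L1 as the test of the central hypothesis.
3. For every outcome with a baseline measurement, report L1 − baseline and L2 − baseline with 95% confidence intervals from the same generalized estimating equations. Do not read a non-significant L1 − baseline result as absence of effect.
4. Word a result as an improvement over lighting as usual only if the intervals for both L2 − L1 and L2 − baseline exclude zero in favour of L2. Otherwise, where L2 − L1 favours L2, word it as better than static lighting kept on while awake.
5. Table 1 lists the Lubben and Lawton-Brody scales only at the end of each condition. Make no claim over usual lighting for them unless a baseline score exists.
6. State that baseline always comes first and lasts about 2 weeks, so L2 − baseline is non-randomised and mixed with time and practice effects.

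The cost is a few sentences and no new data for outcomes already measured at baseline. The claim over usual lighting becomes harder to make. For a true L2 effect equal to the plan's detectable difference, with L1 equal to baseline, the chance of making it falls from about 77% (L2 − L1 significant, baseline–L1 not) to 69%, or to 55% if the baseline variance is doubled. Power for L2 − L1 does not change.

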**Methods:**

This protocol is a randomized, cross-over, single-site trial followed by an exploratory third intervention. Up to 70 older adults in independent living residences at a senior living facility will be recruited. During this 16-week study, participants will experience three lighting conditions. Two cohorts will first experience a static and a dynamic lighting condition in a cluster-randomized cross-over design. The static condition lighting will have fixed brightness and color to match lighting typically provided in the facility. For the dynamic condition, brightness and color will change throughout the day with increased brightness in the morning. After the cross-over, both cohorts will experience another dynamic lighting condition with increased morning brightness to determine if there is a saturation effect between light exposure and health-related measures. Light intake, sleep quality, and physical activity will be measured using wearable devices. Sleep, cognitive function, mood, and social engagement will be assessed using surveys and cognitive assessments.

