### Participants

Initially, up to 100 older adults will be screened into the study based on the inclusion exclusion criteria. However, because we are working with older adults where the incidence of cognitive impairment may be greater, we anticipate that up to 70 individuals will remain eligible after completing the consent capacity assessment (described below). Participants will be asked to allow study staff to install lighting in their residences that can be controlled remotely to produce the different lighting conditions. Up to 35 residences will be outfitted with the lighting systems resulting in between 35 and 70 participants being recruited (depending on whether the residence is single and double occupancy).

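### The power paragraph claims that 0.3 SD is detectable in either enrolment scenario, contradicting its own 0.45 SD for 35 participants, and states no allowance for cohabiting pairs in its 70-participant figure

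*Protocol article*

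**What the plan says.** The power statement is in the Statistical analysis plan section of the protocol article. For the smaller enrolment: "If only 35 participants are enrolled, we expect 80% power to detect a difference of minimum of 0.45 standard deviations". For the larger one: "we expect 80% power to detect a minimum difference of 0.3 standard deviations". The larger scenario is defined as the one in which "all the rooms are double occupancy with both persons eligible". The summary that follows covers both: "For either of these scenarios, we expect to be able to detect at least 0.3 standard deviations, yielding sufficient power". It adds that this holds even for the cognitive assessments, which are the less frequent measurements.

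The Participants section explains where the two enrolment figures come from: "Up to 35 residences will be outfitted with the lighting systems resulting in between 35 and 70 participants being recruited". The number of residences is therefore capped at 35 in both scenarios, and 70 participants means two people in every one of them. The Methods part of the abstract describes the allocation: "Two cohorts will first experience a static and a dynamic lighting condition in a cluster-randomized cross-over design". The power paragraph gives no significance level, sidedness, definition of the SD or within-residence correlation. It justifies generalized estimating equations by the repeated measures and by missing data, and does not mention shared residence.

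**The concern.** If 0.45 SD is the minimum difference detectable at 80% power with 35 people, a difference of 0.3 SD has less than 80% power with the same 35 people. The summary sentence says otherwise, and it is the paragraph's conclusion on whether the trial is large enough. The 35-participant case is not remote. It is the lower end of the planned enrolment, and the Discussion warns that recruitment may be difficult.

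The second part concerns the 70-participant figure. Two people in one home share the intervention and much of their daily routine, so their responses to a change of lighting may be correlated. If they are, 70 people in 35 homes carry less information than 70 unrelated people. The printed figure improves by at least as much as independence would allow.

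At stake is the sensitivity that a reader attributes to the trial, above all if most of the enrolled residences are single occupancy.

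**Working it through.** **Inputs from the Statistical analysis plan and Participants sections.** Power 80%; detectable difference 0.45 SD at n = 35 and 0.3 SD at n = 70; at most 35 residences; the 70-participant case is 35 pairs. **Assumed:** two-sided 5% (one-sided also shown) and a within-residence correlation ρ of the within-person differences between 0 and 0.5.

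**1. Can the printed figures be reproduced?** For a within-person comparison, the detectable difference is (z_α + z_0.80)/√n in units of the SD of the within-person difference. At two-sided 5%, z_α + z_0.80 = 1.96 + 0.84 = 2.80.

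| Basis | n = 35 | n = 70 |
|---|---|---|
| Printed | 0.45 | 0.3 |
| SD of the difference, two-sided 5%, normal (paired t) | 0.474 (0.487) | 0.335 (0.340) |
| SD of the difference, one-sided 5%, normal (paired t) | 0.420 (0.429) | 0.297 (0.300) |
| Raw-outcome SD, two-sided 5%, assumed within-person correlation 0.55: 2.80 × √(2(1 − 0.55)/n) | 0.449 | 0.318 |

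The last row matches both figures to the precision printed. The scale is not stated, so the remaining steps take the plan's 0.45 SD at 80% power as given and do not replace it.

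**2. Power at 0.3 SD with 35 participants, from the plan's own figure.**

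- Two-sided 5%: Φ(2.80 × 0.30/0.45 − 1.96) = Φ(−0.09) = 0.46.
- One-sided 5%: Φ(2.49 × 0.30/0.45 − 1.645) = Φ(0.01) = 0.51.

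The unit of the SD cancels in the ratio 0.30/0.45, so this result does not depend on which SD was meant.

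**3. Participants needed for 0.3 SD at 80% power, on the same basis.** 35 × (0.45/0.30)² = 78.75, about 79 independent participants, against a maximum of 70.

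**4. From 35 to 70 participants.** Doubling independent people shrinks the detectable difference by √2 = 1.41, which takes 0.45 to 0.45/√2 = 0.318. The printed ratio is 0.45/0.3 = 1.5. For clusters of two the design effect is 1 + ρ, so the detectable difference is 0.45 × √((1 + ρ)/2). Power at 0.3 SD (two-sided 5%) is Φ(2.80 × 0.30/difference − 1.96).

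| ρ (assumed) | Detectable difference, 70 people in 35 residences | Power at 0.3 SD |
|---|---|---|
| 0 | 0.32 SD | 75% |
| 0.2 | 0.35 SD | 67% |
| 0.3 | 0.36 SD | 64% |
| 0.5 | 0.39 SD | 58% |

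**5. What rounding could hide.** The 0.3 is printed to one decimal, so it could stand for as much as 0.349. Solving 0.45 × √((1 + ρ)/2) = 0.349 gives ρ = 2 × (0.349/0.45)² − 1 = 0.20.

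**The case against.** The strongest reply concerns the printed figures themselves. A reader might infer from the paired calculation that 0.45 SD is wrong and should be about 0.49 SD, or that 0.3 SD reveals a one-sided test. The document does not support either inference. Both assume that the unit is the SD of the within-person difference, which is not stated, and a raw-outcome SD with a within-person correlation of 0.55 reproduces both figures. An article may also leave significance level, sidedness, SD definition and dropout allowance to the full plan, so their absence is no fault here. That reply stands, and the point makes no use of those absences.

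A reader might also infer that the calculation certainly ignored pairing. This too goes further than the text allows. The printed 0.3 is rounded and could contain a correlation of up to about 0.2. The relevant correlation is that of within-person differences, from which stable similarity between partners cancels, so it may be small. What remains is narrower: the printed figure is as favourable as full independence or more so, and no allowance is stated.

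Finally, the summary sentence is framed around the cognitive assessments, which are secondary outcomes, while the primary sleep outcome is measured daily. Nothing in the article says that a null result will be read as ruling out 0.3 SD. Both remarks are fair and limit the consequences. They do not remove the contradiction, because the 0.45 SD and the summary belong to the same calculation and no separate figure is given for the daily measures. Nor does reading the summary as covering differences of 0.3 SD or larger help: at 35 participants, differences from 0.3 up to 0.45 SD have less than 80% power.

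**Conclusion.** The contradiction is established from the article's own sentences. With 35 participants, 0.3 SD does not have 80% power. On the plan's 0.45 SD basis it has about 46% (two-sided 5%) or 51% (one-sided 5%), and no enrolment allowed by the protocol reaches the 79 independent participants that basis requires. These power values use the normal approximation; the contradiction itself needs no assumption.

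The pairing part is an inference and holds in a limited form. The 70-participant case consists of 35 pairs in a design that the abstract calls cluster-randomized, and no allowance for within-residence correlation is stated. Scaling 0.45 SD gives 0.32 SD at best and 0.39 SD at a correlation of 0.5. That range rests on assumed correlations, since the article gives none. The 0.45 SD figure itself is not shown to be wrong.

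**What to change.** In the Statistical analysis plan section:

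- Delete the sentence that claims sufficient power at 0.3 SD in both scenarios.
- State 0.45 SD as the detectable difference at 80% power for 35 participants.
- Restate the 70-participant figure on the same basis with residence as the cluster, as 0.45 × √((1 + ρ)/2), and give the assumed ρ: 0.32, 0.35, 0.36 and 0.39 SD for ρ = 0, 0.2, 0.3 and 0.5. If the original calculation already included a within-residence correlation, state its value and print the detectable difference to two decimals.
- Do not replace 0.45 SD with a figure such as 0.49 SD, because the SD scale and sidedness behind the printed values are not given.

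The cost is one rewritten paragraph. It needs no extra participants and no change to the design. The only downside is a less favourable stated sensitivity.
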